#### Upstream mechanisms

*Family functioning* will be assessed using an adapted version of the Systemic Clinical Outcome and Routine Evaluation-15 (SCORE-15) (Stratton et al., 2010), which has shown good psychometric properties in previous studies with similar populations (Hamilton et al., 2015), including adequate internal consistency in the feasibility study (*α* = 0.80) (Brown et al., 2024). One additional item about satisfaction with family decision-making was added during the feasibility study and has been retained. The adapted version of the SCORE-15 will be reported by both adolescents and caregivers, with adolescent-report used to assess primary effectiveness.

*Parenting practices* will be evaluated through the Arabic Dimension of Parenting Scale (caregiver-report), a 24-item measure addressing parental warmth, positive parenting strategies and harsh discipline practices (Miller et al., 2020). One additional item on parental problem-solving was added during the feasibility study and has been retained.

*Caregiver mental health* will be measured with the K10, a brief 10-item scale screening for psychological distress (Kessler et al., 2003), while *mental well-being* will be assessed using the Warwick-Edinburgh Mental Wellbeing Scale (WEMWBS) (Stewart-Brown and Janmohamed, 2008).

#### Downstream adolescent outcomes (index adolescent)

*Adolescent mental health* will be assessed using the SDQ reported by both adolescents (Alyahri and Goodman, 2006) and caregivers (Goodman, 2001). Primary effectiveness will be assessed by adolescent-report.

*Well-being* will also be assessed using the same WEMWBS scale as administered to caregivers, providing parallel measurement across family members, as well as the Children’s Hope Scale (Snyder et al., 1997).

Additional exploratory outcomes, sociodemographic characteristics and implementation data will also be collected and are outlined in Table 3. These variables will also be controlled for in effectiveness analyses to account for variation over time.

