#### Enhanced treatment as usual (ETAU)

The control condition will be an ETAU consisting of one 30–45 min session comprising a structured, family psychoeducation session delivered by a non-specialist facilitator to the participating caregivers and index adolescent. The scripted session consists of (1) sharing the screening results with the family; (2) discussing common and simple self-care strategies to manage distress; and (3) providing information about available MHPSS, caregiving and financial literacy resources and services. The ETAU will be delivered by non-specialist facilitators, who are different from the StrongerTogether facilitators and who receive a separate 1-day training on the delivery of the psychoeducation session.

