#### Randomisation

Randomisation will occur after baseline assessments. Families will be randomly allocated to treatment or ETAU conditions in a 1:1 ratio. A computer-generated randomisation sequence will be created by an independent statistician external to the study location using Research Randomizer (randomizer.org). Complete, temporal participant lists will be provided to the independent statistician, who will match them to the randomisation sequence and return allocations for implementation.

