#### Masking

All investigators and research assistants will be masked to the allocations of families. Due to the nature of the intervention, complete masking of participants and implementation staff is not possible. Staff will receive training on maintaining masking protocols during data collection, research and implementation teams will operate separately, and participants will be instructed not to reveal their allocation. Research assistants will document instances where allocation is accidentally revealed. The level of (un)masking of the research assistants will be assessed at the end of each follow-up interview by asking research assistants if allocation was explicitly revealed during the interview. These data will be used to assess the integrity of masking and to control for possible bias in impact analyses, in addition to being reported as a study limitation.

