** *Implementation and process evaluation measures* **			
Proactive family-level case detection	ReachNow family version	Illustrated vignettes showing a prototype family experiencing multiple psychosocial and financial challenges Simple decision algorithm to identify families in need of mental health care Used by community outreach staff for family identification	Approximately 70% of children identified using the tool were confirmed in need of mental healthcare in clinical assessment in Sri Lanka and Palestine (van den Broek et al., 2021, 2023); an adapted tool was piloted with 78 families in Jordan during feasibility study
Facilitator competency	Family Act Tool (FamilyACT) (WHO, 2025)	Observational rating tool for MHPSS interventions delivered by non-specialists Developed for the World Health Organization EQUIP (Ensuring Quality in Psychological support initiative) platform Adequate single-rater reliability (ICC: 0.40) Sensitivity to change over time (Wilcoxon signed-rank tests, *α* < 0.05)	Developed for interventions where non-specialists deliver MHPSS interventions (Kohrt et al., 2025); with similar tools used in previous studies with high inter-rater reliability (ICC: 0.71–0.89) (Pedersen et al., 2021; Mwenge et al., 2022), single-rater reliability (ICC: 0.41–0.75) and demonstrated sensitivity to change (Jordans et al., 2021)
Implementation fidelity	Module completion, supervisor observation and programme monitoring and supervision records	Programme monitoring Documentation of supervisor observations Debrief meetings on facilitator module completion and implementation Fidelity will be calculated as the percentage of core components delivered as intended following session observations by the supervisor	NA
Implementation acceptability and potential for scale	Module attendance, acceptability and barriers and facilitators to implementation	Documentation of module completion and session participation per family member, with reasons for non-attendance recorded Qualitative focus groups and interviews	NA
Process documentation	Programme monitoring and debrief notes	Programme monitoring Debrief meetings on progress and challenges with outreach, family module completion and implementation	NA

**Table 4. tab4:** Process evaluation outcomes and measures for implementation, effectiveness and potential sustainability by the RE-AIM framework

Dimension	Study definition	Participant level	Organisation level

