### Statistical analysis

#### Effectiveness analyses

Trial results will be reported following the updated recommendations of the Consolidated Standards of Reporting Trials (CONSORT) 2017 statement for randomised trials of nonpharmacologic treatments (Boutron et al., 2017). All analyses will use an intent-to-treat approach, including all randomised participants regardless of intervention adherence. Statistical significance will be evaluated with a significance level of *p* < 0.05 for each step, with analyses proceeding regardless of preceding step results to fully understand intervention mechanisms.

*Primary effectiveness analyses* will test dual outcome hypotheses sequentially to examine intervention effects on upstream and downstream outcomes using hierarchical linear modelling to account for the nested data structure: (1) repeated measurements within individuals; (2) multiple individuals nested within families; and (3) families randomised to intervention or control conditions. T2 is the primary time point for evaluating intervention effects using group × time interactions, accounting for individual-level fixed effects (*e.g.*, age, gender and baseline measures) and random effects at the individual and family levels (*e.g.*, variation in stress over time).

*Secondary exploratory analyses* will test moderation effects and employ latent growth curve modelling to investigate treatment response patterns and mechanisms of change. Sub-group analyses will examine differential effects by facilitator characteristics, module completion and family and individual characteristics, including time since displacement. Sensitivity analyses will include per-protocol analyses limited to participants completing sufficient dosage of core sessions and alternative missing data approaches.

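### The protocol says effectiveness models will control for exploratory outcomes and implementation data, which arise or can change after randomisation, so the group × time coefficient would not estimate the promised intent-to-treat effect

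*Protocol article*

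**What the plan says.** All places are in the protocol article.

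- **Downstream adolescent outcomes (index adolescent).** The variables are introduced thus: "Additional exploratory outcomes, sociodemographic characteristics and implementation data will also be collected and are outlined in Table 3". The next sentence gives their use: "These variables will also be controlled for in effectiveness analyses to account for variation over time".
- **Table 3, implementation and process evaluation measures.** One entry under implementation data reads: "Documentation of module completion and session participation per family member, with reasons for non-attendance recorded".
- **Randomisation.** "Randomisation will occur after baseline assessments". Anything recorded at T1, T2 or T3 is therefore post-randomisation.
- **Enhanced treatment as usual (ETAU).** "The control condition will be an ETAU consisting of one 30–45 min session". Control families are offered no modules.
- **Effectiveness analyses.** The primary analysis is a hierarchical linear model with a group × time interaction, "accounting for individual-level fixed effects (*e.g.*, age, gender and baseline measures"). The approach is intent-to-treat and keeps every randomised participant, whatever their adherence.
- **Masking.** "The level of (un)masking of the research assistants will be assessed at the end of each follow-up interview". Of the resulting data the protocol says: "These data will be used to assess the integrity of masking and to control for possible bias in impact analyses".

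**The concern.** Covariates in a randomised comparison should be fixed before allocation. A variable that allocation can change is part of the result, and holding it constant removes whatever part of the effect runs through it. It can also add bias through unmeasured causes shared by that variable and the outcome.

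The sentence in the Outcomes section directs the analyst to include such variables. At stake is the primary contrast. H1 is the only hypothesis the protocol describes as fully powered, and the effect it is designed to detect is small (d = 0.15). The intent-to-treat statement would still describe who is analysed, but the coefficient would answer a different question: the difference between arms at equal levels of attendance or of other outcomes.

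**Working it through.** **1. Can the sentence be read as baseline-only?**

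- Its stated purpose is to allow for variation over time. A single T0 value does not vary over time. Under Data collection, outcome measures and putative mediators are collected at T0, T1, T2 and T3, so time-varying values will be available.
- Implementation data have no T0 value. Attendance and module completion begin after allocation, and control families have one session and no modules.
- Sociodemographic characteristics do have T0 values. Adjusting for those is legitimate and is not in dispute.

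A baseline-only reading therefore fails for implementation data, and nothing in the text imposes it on the exploratory outcomes.

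**2. Does the statistical section override it?**

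Its named fixed effects (age, gender, baseline measures) are all pre-randomisation, but they are given as examples. Nothing there withdraws the sentence in the Outcomes section, so the two places conflict.

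**3. Illustration: one post-randomisation outcome as covariate.**

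The protocol gives no figure for this bias, so there is none to reproduce. From the protocol (Sample size): d_Y = 0.15, used only as the scale of the effect. Assumed: the intervention shifts covariate M by d_M; the within-arm SDs of Y and M are 1; their within-arm correlation is r; both are coded so that higher is better; there is a single follow-up time.

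In a linear model of Y on arm and M, the slope on M is r, so

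adjusted arm effect = d_Y − r × d_M.

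| r | d_M = 0.15 | d_M = 0.30 |
|---|---|---|
| 0.3 | 0.15 − 0.045 = 0.105 | 0.15 − 0.09 = 0.06 |
| 0.5 | 0.15 − 0.075 = 0.075 | 0.15 − 0.15 = 0.00 |
| 0.7 | 0.15 − 0.105 = 0.045 | 0.15 − 0.21 = −0.06 |

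A simulated regression (N = 1,000,000, r = 0.5, d_M = 0.15) gave 0.151 unadjusted and 0.075 adjusted, in agreement with the formula. With T0 covariates only, the coefficient keeps the full 0.15 in expectation.

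**4. Illustration: attendance as covariate.**

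Assumed: intervention families attend each of the seven core sessions with probability 0.75 (mean 7 × 0.75 = 5.25), controls are coded 0, and benefit is proportional to sessions attended.

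- Variance of attendance between arms: 0.25 × 5.25² = 6.89. Within arms, averaged over the two: 0.5 × 7 × 0.75 × 0.25 = 0.66.
- R² of arm with attendance = 6.89 / (6.89 + 0.66) = 0.913.
- Variance inflation for the arm term = 1 / (1 − 0.913) ≈ 11.5.
- Simulated arm effect: 0.152 unadjusted, 0.003 adjusted. The effect moves to the attendance slope (0.028 per session, against 0.15 / 5.25 = 0.029 put in).

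The near-zero arm term follows from the proportional-benefit assumption. The near-collinearity of arm and attendance does not depend on it.

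**The case against.** The strongest reply is that one sentence in the Outcomes section is not the model specification. The statistical section names only pre-randomisation covariates, and the protocol already gives implementation data other roles. Effectiveness analyses places module completion in sub-group analyses and core-session dosage in a per-protocol sensitivity analysis. Table 4 lists moderation and exploratory mediation, and Process evaluation uses attendance and completion. The authors may well intend a baseline-adjusted primary model. That is a fair guess at intent, but the text says otherwise and nothing retracts it. Nor is this detail left to an analysis plan: it is a rule that the article states.

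Four stronger readings might be inferred, and the documents do not support them.

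- *Unmasking is a covariate in the primary model.* The Masking section speaks of controlling for possible bias in impact analyses but does not name the primary model, and a sensitivity analysis fits its wording. The protocol also does not say that allocation will be revealed more often in the intervention arm. This calls for clarification only.
- *The coefficient is uninterpretable, or biased toward the null.* It would have a meaning, though not as the intent-to-treat effect. The direction of bias cannot be derived from the documents.
- *Adjusting for attendance gives zero by construction.* That holds only if benefit is proportional to sessions attended; otherwise the term can differ from zero in either direction.
- *Well-being and fidelity are among the variables to be adjusted for.* Well-being is named just before the text turns to additional outcomes. Fidelity comes from supervisor observation of sessions and is not presented as a family-level covariate. Emotion regulation and financial literacy are plausible members of the set, but Table 3 lists them as secondary and has no heading for exploratory outcomes.

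**Conclusion.** The sentence is wrong as written. Followed literally, it puts consequences of allocation into the effectiveness models and conflicts with the intent-to-treat effect promised under Effectiveness analyses. The case is firmest for attendance and module completion, which cannot be baseline variables. For exploratory outcomes it rests on the absence of any restriction to T0 and on the stated purpose.

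The structural fault does not depend on any assumed number; the size of the bias does. The drop from 0.15 to 0.105, 0.075 or 0.045 rests on assumed correlations and an assumed equal shift in the covariate, and shows only that one such covariate could remove a large share of an effect of the size planned for. The sentence should be corrected before the primary model is fixed.

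**What to change.** Replace the sentence in Downstream adolescent outcomes with text such as:

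> *Effectiveness models adjust only for covariates measured at T0 (baseline outcome, age, gender, baseline sociodemographics). As explanatory variables, post-baseline outcomes and implementation data are used only in the mediation, moderation, sub-group, per-protocol and process analyses described in Table 4, Effectiveness analyses and Process evaluation.*

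The list in the second sentence matters. A restriction to process and mediation analyses alone would contradict the sub-group and per-protocol uses already planned. Moderation must stay in the list because H3 itself relates adolescent mental health to post-baseline upstream improvement.

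In Masking, add that unmasking is reported by arm and used only in a labelled sensitivity analysis.

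The cost is two short edits to the protocol. No change to data collection, sample size or staffing is needed.

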#### Implementation tool evaluation

The *accuracy of case detection* of the ReachNow family tool will be validated by comparison against the screening results. Sensitivity, specificity, positive predictive value and negative predictive value of the ReachNow tool will be calculated using the screening results as the standard.

*Facilitator competency* will be assessed using the FamilyACT tool, an observational rating scale based on existing tools within the World Health Organization Ensuring Quality in Psychological Support (WHO EQUIP) platform for assessing competencies of non-specialists delivering MHPSS interventions (WHO, 2025), and adjusted for whole-family interventions during earlier studies in Lebanon (Brown et al., 2022) and Jordan (Brown et al., 2024). The tool assesses common competencies for working with families across 15 domains, with reliability across contexts (Kohrt et al., 2025). Each facilitator will be observed and rated by a trained competency rater at four timepoints: (1) during the training (days 2 or 3), (2) during the post-training practice round, (3) early intervention (sessions 1 or 2) and (4) after completion of the seven core sessions. The reliability of the tool will be assessed by calculating internal consistency (Cronbach’s 𝛼 ≥ 0.70) and single rater-reliability (single measures intraclass correlation coefficient ≥ 0.40) at each time point. The tool’s sensitivity to change will also be evaluated through measurement of facilitators’ competencies across timepoints through statistical testing using Wilcoxon signed-rank tests (*W*) (*α* < 0.05) to evaluate changes in levels of competencies for the newly trained facilitators over time.

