#### Primary implementation hypotheses

The ReachNow tool will accurately identify 70% or more of families in need of focused mental health support as identified through screening results. In addition, the FamilyACT tool will demonstrate adequate reliability and validity for assessing facilitator competencies in delivering family-systemic interventions in humanitarian settings.

The study will secondarily explore mechanisms of change of the intervention through mixed-methods exploratory longitudinal analyses.

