### Procedures

#### Recruitment, informed consent and data collection

##### Pre-study evaluation of ReachNow detection tool

To recruit families, outreach staff will be trained to use an adapted version of ReachNow, a proactive community case detection tool (van den Broek et al., 2023). The proactive case detection approach employs illustrated vignettes depicting a family experiencing multiple psychosocial challenges (including mental health difficulties, family conflict and financial stress). The simple decision algorithm asks outreach staff to assess whether the depicted family resembles families they know in their community who might benefit from focused mental health support. If they identify similarities, they are prompted to refer those families for assessment. Previous versions of the child-focused tool demonstrated 70% accuracy compared to clinical assessment in Sri Lanka and Palestine (van den Broek et al., 2021, 2023). The family-adapted version was piloted in Jordan during the feasibility study with 78 families, demonstrating feasibility and appropriateness. In the present study, the tool will be formally evaluated for accuracy.

War Child Jordan will identify and train outreach staff on the participant inclusion/exclusion criteria and how to use the family version of the ReachNow detection tool to identify families who are eligible for the intervention. These individuals are trusted and respected community members who have established and regular communication with families who are struggling, including personnel and volunteers. During outreach for study enrolment, the family version of the ReachNow tool will be evaluated for accuracy by comparing the ReachNow caseness with screening outcomes assessing mental health challenges (caregiver and child), family functioning difficulties, parenting challenges and financial stress in accordance with study inclusion criteria.

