##### Recruitment

Recruitment will be led by outreach staff under the supervision of War Child Jordan during the study enrolment period using the family version of the ReachNow detection tool. Outreach staff will contact families who meet the eligibility criteria, inform them about the intervention using a script and offer an invitation to participate. Those families who confirm interest will be asked for verbal consent and then referred to the research team for the screening assessment.

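### As described, only ReachNow-positive families reach screening, so of the four planned accuracy measures only positive predictive value is estimable, while the 70% hypothesis is worded as a sensitivity

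*Protocol article*

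**What the plan says.** The hypothesis, under Primary implementation hypotheses, is: "The ReachNow tool will accurately identify 70% or more of families in need of focused mental health support as identified through screening results". The analysis, under Implementation tool evaluation, is: "Sensitivity, specificity, positive predictive value and negative predictive value of the ReachNow tool will be calculated using the screening results as the standard".

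The route to screening is set out under Procedures. Outreach staff compare families they know with an illustrated vignette: "If they identify similarities, they are prompted to refer those families for assessment". Recruitment runs "during the study enrolment period using the family version of the ReachNow detection tool". Two further filters follow before screening: "Outreach staff will contact families who meet the eligibility criteria", and "Those families who confirm interest will be asked for verbal consent and then referred to the research team for the screening assessment". The accuracy comparison is placed in this same stream: "During outreach for study enrolment, the family version of the ReachNow tool will be evaluated for accuracy by comparing the ReachNow caseness with screening outcomes". The Screening section then describes the interview, given by research assistants, that serves as the reference.

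Table 3 gives the earlier performance of the child version: "Approximately 70% of children identified using the tool were confirmed in need of mental healthcare in clinical assessment". The Procedures text calls the same 70% accuracy, without a denominator.

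**The concern.** Sensitivity, specificity and NPV all need families who were judged ReachNow-negative and were then screened. The article describes no such families. A two-by-two table filled only from referred families has an empty test-negative row, and three of the four planned measures then carry no information about the tool.

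Separately, the hypothesis and its benchmark share the figure of 70% but not the denominator. The hypothesis asks what share of families in need the tool finds. The benchmark reports what share of those found were in need. A tool can do well on one and badly on the other.

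At stake is a hypothesis labelled primary for implementation, in an article that promises validated tools ready for use by other organisations. A sensitivity reported from this flow would look like strong evidence and would be an artefact of who was screened.

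**Working it through.** The 70% is a threshold, not a derived figure, so there is nothing to reproduce. The check is two-by-two algebra, with TP, FP, FN and TN defined against the screening result.

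**Formulas**
- Sensitivity = TP/(TP+FN)
- Specificity = TN/(TN+FP)
- PPV = TP/(TP+FP)
- NPV = TN/(TN+FN)

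**Step 1: the described flow.** Only referred families are screened, so FN = TN = 0.
- Sensitivity = TP/(TP+0) = 100%
- Specificity = 0/(0+FP) = 0%
- NPV = 0/0, undefined
- PPV = TP/(TP+FP), estimable

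To put numbers in, assume 786 families screened. The documents do not give the number screened; 786 is 550/0.70 rounded up, and serves only for scale.

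| Assumed TP / FP | PPV | Sensitivity | Specificity | NPV |
|---|---|---|---|---|
| 550 / 236 | 70% | 100% | 0% | undefined |
| 393 / 393 | 50% | 100% | 0% | undefined |

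A tool that is wrong for half the families it flags still passes a 70% sensitivity threshold.

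**Step 2: what the unscreened families could hide.** Keep TP = 550 and FP = 236 (PPV 70%). Assume a number of ReachNow-negative families and a prevalence of need among them. Neither is in the documents.

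| Unscreened negatives | Need among them | FN | True sensitivity | True specificity |
|---|---|---|---|---|
| 200 | 5% | 10 | 550/560 = 98% | 190/426 = 45% |
| 786 | 20% | 157 | 550/707 = 78% | 629/865 = 73% |
| 786 | 40% | 314 | 550/864 = 64% | 472/708 = 67% |
| 2000 | 20% | 400 | 550/950 = 58% | 1600/1836 = 87% |
| 5000 | 20% | 1000 | 550/1550 = 35% | 4000/4236 = 94% |

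Every row gives the same observed data. True sensitivity drops below 70% once FN exceeds 550 × 0.30/0.70 = 235.7, that is, at about 236 missed families. The described data cannot show whether that has happened.

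**Step 3: the denominators side by side.**
- Hypothesis: the denominator is families in need according to screening, TP+FN. This is sensitivity.
- Table 3 benchmark: the denominator is children identified by the tool, TP+FP. This is PPV.

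This mismatch stands however ReachNow-negative families are handled.

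**Step 4: precision of the PPV, as illustration only.** With 786 independent families and PPV 0.70, the 95% half-width is 1.96 × √(0.70 × 0.30/786) = 0.032. Each outreach worker judges several families, so independence is doubtful. If each worker referred 30 families with an intra-worker correlation of 0.05 (both assumed), the design effect is 1 + 29 × 0.05 = 2.45 and the half-width is 0.032 × √2.45 = 0.050.

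**The case against.** The strongest objection is that the article nowhere says ReachNow-negative families go unscreened. It says that matching families are referred and is silent on the rest. The tool evaluation has its own sub-heading, marked as pre-study, and a plan for all four measures may imply that the full protocol samples negatives. This stands in part: positives-only screening is an inference, and a reader should not conclude that the documents rule out a negative sample. But the text under that sub-heading places the comparison within enrolment outreach, and the steps it describes lead from tool to referral to screening. The planned measures and the described procedure do not match, and the denominator mismatch is unaffected.

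A second objection is that the sponsor may intend the 70% as a PPV, which is already among the planned measures and can fail. That is plausible given Table 3. It makes the defect one of wording, and automatic confirmation follows only from the literal reading.

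Two stronger readings should be resisted. Because outreach staff are trained on the eligibility criteria, a reader might infer that the index test is partly its own reference standard. The documents do not support this: the reference is a separate interview using the K10, the caregiver-report SDQ and structured questions, given by research assistants. The training changes what is tested (the tool plus training) and who is screened; it does not put the ReachNow result into the reference. A reader might also infer that the PPV will be precise to about 3 points. The number screened is not given. The 786 also rests on enrolled families, counted after exclusions, so it does not match a reference-positive state defined before them, and it ignores clustering.

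**Conclusion.** The point holds for the flow as described. Three of the four planned measures are not estimable (100%, 0% and undefined by construction), and only PPV carries information. The hypothesis is worded as a sensitivity, its benchmark is a PPV, and on the literal wording it would be met whatever the tool's quality. The algebra needs no assumption beyond the absence of screened ReachNow-negative families, which is inferred from the Procedures section. The sensitivities of 35% to 98% and the half-widths of 3 to 5 points are illustrations on assumed inputs.

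This should be fixed, but it does not threaten the trial. The article places the tool evaluation second to the effectiveness aim, and the test of H1 is unaffected.

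**What to change.** 1. Restate the hypothesis under Primary implementation hypotheses as: at least 70% of ReachNow-identified families are confirmed in need by screening (PPV). Report it with a confidence interval that allows for clustering by outreach worker.
2. Remove sensitivity, specificity and NPV from Implementation tool evaluation. The exception is if the full protocol already screens a sample of ReachNow-negative families. In that case state so, give the sampling fraction, and weight the estimates by it.
3. Define reference-positive as meeting the need criteria under Participant inclusion/exclusion criteria (A and/or B, plus at least one of C to E) before the safety and severity exclusions. Otherwise families with greater need would count as false positives.
4. State that the PPV describes the tool as used by staff trained on the eligibility criteria, among families willing to be screened.

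The cost is a few sentences of wording. The sponsor gives up a sensitivity claim that the described design cannot support.
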